# Footwear, foot orthoses and strengthening exercises for the non-surgical management of hallux valgus: protocol for a randomised pilot and feasibility trial

**DOI:** 10.1186/s13047-022-00553-4

**Published:** 2022-06-03

## Abstract

**Background:**

Hallux valgus is a common and disabling condition. This randomised pilot and feasibility trial aims to determine the feasibility of conducting a fully-powered parallel group randomised trial to evaluate the effectiveness of a multifaceted non-surgical intervention for reducing pain associated with hallux valgus.

**Methods:**

Twenty-eight community-dwelling women with painful hallux valgus will be randomised to receive either a multifaceted, non-surgical intervention (footwear, foot orthoses, foot exercises, advice, and self-management) or advice and self-management alone. Outcome measures will be obtained at baseline, 4, 8 and 12 weeks. The primary outcome is feasibility, which will be evaluated according to demand, acceptability, adherence, adverse events, and retention rate. Limited efficacy testing will be conducted on secondary outcome measures including foot pain (the Manchester-Oxford Foot Questionnaire), foot muscle strength (hand-held dynamometry), general health-related quality of life (the Short Form-12), use of cointerventions, and participants’ perception of overall treatment effect. Biomechanical testing will be conducted at baseline to evaluate the immediate effects of the footwear/orthotic intervention on pressure beneath the foot and on the medial aspect of the first metatarsophalangeal joint and hallux.

**Discussion:**

This study will determine the feasibility of conducting a fully-powered randomised trial of footwear, foot orthoses, foot exercises, advice and self-management for relieving pain associated with hallux valgus and provide insights into potential mechanisms of effectiveness.

**Trial registration:**

Australian and New Zealand Clinical Trial Registry (ACTRN12621000645853).

**Supplementary Information:**

The online version contains supplementary material available at 10.1186/s13047-022-00553-4.

## Background

Hallux valgus is a common and disabling condition characterised by the lateral deviation of the hallux towards the lesser toes. A systematic review of population-based studies (total 496,957 participants) reported pooled prevalence estimates of 23% in people aged 18 to 65 years and 36% in people aged over 65 years [1], with women twice as likely to be affected. The progressive subluxation of the first metatarsophalangeal joint and formation of an osseus prominence on the medial aspect of the first metatarsal leads to crowding and deformity of the lesser toes [2], abnormal gait patterns [3], impaired balance [4], difficulties with finding comfortable footwear [5], an increased risk of falls in older people [6] and decreased health-related quality of life [7].

The impact of hallux valgus on the healthcare system is considerable, as it is a frequent presentation in primary care and is one of the most common conditions treated by podiatrists [8] and orthopaedic surgeons [9]. A recently published analysis of 1.6 million patient-encounter records from the Bettering the Evaluation and Care of Health primary care dataset revealed that general practitioners (GPs) in Australia encounter an estimated 60,000 cases of hallux valgus every year (an approximate cost of AU$2.2 M in Medicare subsidies for initial GP consultations alone [10]) while Medicare Benefits Schedule data indicates that approximately 7,000 hallux valgus surgical procedures are performed by orthopaedic surgeons in the private sector per year, at an estimated cost of AU$3 million [11]. Although substantial, this is an underestimate of the true economic burden of hallux valgus surgery, as many procedures are also performed in public hospitals and by podiatric surgeons [12].

Despite the high prevalence, associated impairments in quality of life and economic burden of hallux valgus, there are no widely adopted, evidence-based clinical guidelines to inform the selection of the most appropriate interventions. In the United Kingdom, the National Institute for Health Care Excellence (NICE) [13] recommend that people with hallux valgus should first be provided with analgesia, footwear advice, bunion splints or orthoses. If these treatments are not effective or the severity of the condition progresses, surgical referral is then recommended. However, the NICE guidelines caution that these recommendations are based primarily on expert opinion rather than evidence. In Australia, where no such guidelines exist, people with painful hallux valgus presenting to GPs are most commonly provided with advice, pain medications and referral to orthopaedic surgeons [10].

Non-surgical management of hallux valgus may involve footwear advice or modification, foot orthoses, night splints, and physical therapies (manual therapy, taping or foot exercises). In podiatric clinical practice, these interventions are often combined in a multifaceted approach [14]. However, there is limited evidence for the effectiveness of any of these interventions. A recent systematic review and meta-analysis of non-surgical interventions for hallux valgus identified 16 parallel-group and crossover studies evaluating a wide range of non-surgical interventions [15]. Overall, included trials were of low methodological quality. Many had small sample sizes (12 out of 16 studies having < 60 participants) and short follow-up periods (10 out of 16 having follow-up < 3 months), thus providing low certainty as to the effectiveness of non-surgical interventions and longer-term management of the condition.

Of the available non-surgical treatments, the most widely used are footwear, foot orthoses and foot exercises [14], and there is preliminary evidence supporting the use of these approaches. Ill-fitting footwear is an important modifiable risk factor for the development and progression of hallux valgus, as it has been shown that the likelihood of having the condition is significantly greater in those who have worn shoes with a very narrow toe box between the ages of 20 and 29 years [16]. Furthermore, if the condition is already present, the provision of extra-depth footwear which accommodates the broader forefoot may reduce pain [17]. Foot orthoses have been shown to reduce load under the great toe and medial midfoot in people with hallux valgus [18], and a randomised trial reported a significant reduction in pain at six months those who received this intervention [19]. As hallux valgus progresses, the malalignment of the first metatarsophalangeal joint results in decreased muscle size [20] and subsequent weakness of the muscles responsible for hallux plantarflexion and abduction [21]. However, a recent trial of older people (78% women) found that a progressive, resistance exercise program improved hallux plantarflexion strength by approximately 20% over 12 weeks and resulted in an improvement in perceived foot health [22].

The available evidence provides preliminary support for the use of footwear, foot orthoses and foot exercises for the treatment of hallux valgus, but these three promising approaches are yet to be evaluated in combination. Therefore, the primary objective of this study is to evaluate the feasibility of conducting a randomised trial comparing multifaceted, non-surgical intervention (footwear, foot orthoses, foot exercises, advice, and self-management) versus advice and self-management alone for reducing pain associated with hallux valgus. The secondary objective is to obtain statistical parameters to inform the main trial sample size calculation and provide a signal of efficacy to justify the future main trial.

## Methods

### Study design

The multifaceted inte﻿rve﻿ntion for hallux valgus (MARVELL) trial will be a parallel group, participant- and assessor-blinded, randomised pilot and feasibility trial over 12 weeks. We consider the trial to be both a *pilot* trial (as it includes the key features of a full randomised trial but on a smaller scale) and a *feasibility* trial (as it addresses questions regarding whether a full trial could be feasibly undertaken) [23]. The study has been registered with the Australian and New Zealand Clinical Trial Registry (ACTRN12621000645853), and was developed in consultation with the Standard Protocol Items: Recommendations for Interventional Trials (SPIRIT) 2013 statement [24] and the CONSORT 2010 statement extension to randomised pilot and feasibility trials [25]. The SPIRIT checklist is provided in the Supplementary file, supplemented by items from CONSORT, as recommended by Thabane and Lancaster [26]. Ethical approval was obtained from the La Trobe University Human Ethics Committee (reference number: HEC20474).

### Participants

Twenty-eight participants will be recruited from the northern suburbs of Melbourne, Victoria, Australia. To be eligible for inclusion, participants must: (i) be aged ≥ 40 years, (ii) be female, (iii) have pain in the big toe joint/s (i.e. first metatarsophalangeal or interphalangeal) for at least 12 weeks, (iv) have big toe joint pain rated at least 3 out of 10 on a numerical rating scale, (v) be able to walk household distances (more than 50 m) without the aid of a walker, crutches or cane, (vi) be capable of understanding the English language in verbal and written form, and (vii) have at least moderate hallux valgus on one or both feet, defined as a score of 2 or more on the validated Manchester scale [27], a tool containing four standardised photographs of varying degrees of hallux valgus deformity. Participants will not be eligible for inclusion if they self-report: (i) surgical treatment for hallux valgus on either foot, (ii) lower limb or partial foot amputation, (iii) an inflammatory rheumatological condition such as gout, rheumatoid arthritis, psoriatic arthritis, axial spondyloarthropathy or connective tissue disease, (iv) a neurological disease which interferes with walking (e.g. Parkinson’s disease), (v) having worn arch-contouring foot orthoses in the past 12 weeks (although flat insoles will be permitted), (vi) performing foot exercises (stretching, mobilisation or strengthening) in the past 12 weeks, or (vii) an injury of lower limb(s) or back that may interfere with reaching their feet. We specifically focused on females in this study due to their higher prevalence of hallux valgus [1] and use of constrictive footwear [28].

### Sample size

This is a pilot and feasibility trial, so it is not fully powered to detect statistically significant differences between the groups. The recommended sample size for feasibility and pilot studies is 12 people per group [29], however to allow for a 15% drop-out rate, we will recruit 28 participants. This is similar to the median sample size of 30 for pilot trials documented in the United Kingdom Clinical Research Network database [30].

### Recruitment and screening

Participants will be recruited using the following methods: (i) postal invitation using a database of patients who receive podiatry treatment at the La Trobe University Health Sciences Clinic, (ii) email distribution to staff members in the School of Allied Health, Human Services and Sport at La Trobe University, (iii) Facebook advertising and (iv) posters placed in the local community. Potential participants will be asked to contact the chief investigator ([name]) to express their interest and will then be screened for eligibility by telephone and/or email by two members of the research team ([name] and [name]).

### Baseline assessments

Participant characteristics will be collected by structured interview at the baseline assessment (approximate duration of two hours) and will include age, height, weight, country of birth, education level, major medical conditions, and medications. The following questionnaires and clinical assessments will also be conducted:(i)the Manchester scale [27] for hallux valgus;(ii)foot pain characteristics, including duration and location, using a standardised foot diagram [31];(iii)history of hallux valgus, including age of onset, family history and previous treatments;(iv)shoe-wearing history, using a standardised set of images depicting toe-box shapes and heel heights [16];(v)foot structure, using a 3D laser scanner (INFOOT, I-Ware Laboratory, Japan);(vi)the Incidental and Planned Activity Questionnaire [32];(vii)the Credibility/Expectancy Questionnaire [33], which assesses participants’ beliefs about the logic underpinning the intervention and perceptions of how much they may benefit. The CEQ will be administered after randomisation and allocation. The CEQ consists of six items; three are related to credibility and three are related to expectancy. For each item, participants will be asked to rate the credibility of the intervention and their expectations on a 9-point Likert scale. High scores on the scale indicate that the participant considers the intervention to be credible and expects it to be effective.

### Randomisation

Permuted block randomisation will be used to randomise participants on a 1:1 ratio to the control or intervention group using an online randomisation service (www.sealedenvelope.com).

### Study procedure

Participant flow through the trial is outlined in Fig. 1. All face-to-face assessments will be performed in the Foot and Ankle Laboratory at La Trobe University, Melbourne, Victoria, Australia. Postal follow-ups will be conducted at 4 and 8 weeks, with the final face-to-face follow-up at 12 weeks.

**Fig. 1 Fig1:**
[figure not shown]
Planned participant flow through the trial

### Blinding

Participants will be blinded to group allocation by limited disclosure, in that they will be told that the clinical trial is comparing two non-surgical treatments for hallux valgus, but they are not informed about the specific characteristics of the treatments. Research staff administering the treatments cannot be blinded. Outcomes are participant-reported, thus this study is also assessor-blinded (as participants are blinded). The study biostatistician performing the statistical analyses will be blinded.

### Interventions﻿

#### Control group

The control group will receive a self-management package based on United Kingdom National Health Service recommendations [34] which advise people with hallux valgus to wear wide shoes with a low heel and soft sole, apply cold-packs and silicone gel bunion pads, and use paracetamol for pain relief. To address expectations to be provided with a ‘take-home’ intervention, we will provide all participants with cold-packs (Hot + Cold Therapy Gel Pack; OAPL, Clayton, Victoria, Australia) and silicone gel bunion pads (Spandex Gel™ Cushion Bunion Pads; Neat® Feat, Auckland, New Zealand). To meet ethical guidelines and aid retention, on completion of the study the control group participants will be offered the same treatment as the intervention group.

#### Intervention group

The intervention group will be provided with the same advice and self-management package as the control group, in addition to:(i)Footwear: high quality, off-the-shelf footwear (Anodyne #45 Sport Jogger; Global Footcare, Coomera, Queensland, Australia). These shoes have been selected as they have an extra-wide toe box and pliable upper material to alleviate pressure on the hallux (Fig. 2). The shoes will be correctly fitted by a research podiatrist, and participants will be asked to wear them as often as possible.(ii)Foot orthoses: prefabricated Formthotics™ (Foot Science International, Christchurch, New Zealand). These orthoses are ¾ length and are constructed from dual-density, closed-cell polyethylene foam (bottom layer 140 kg/m^3^, top layer 60 kg/m^3^). See Fig. 3. Previous research has shown that these orthoses are well accepted, with 81% of participants reporting being ‘somewhat or very satisfied’ with them in a 12 month falls prevention trial [35]. We will use the ¾ length rather than full-length devices as they are less likely to increase dorsal/medial pressure from footwear in people with hallux valgus [36]. The existing insoles will be removed from the shoe to accommodate the orthoses. Participants will be asked to wear these with their footwear as often as possible. At the baseline appointment, minor modifications will be made where necessary to ensure that the orthoses are comfortable.(iii)Foot exercises: participants will be provided with access to a smart-phone app (PhysiTrack®, London, United Kingdom) which demonstrates a home-based version of the progressive resistance foot exercise program developed by Mickle et al. [22]. Participants without access to a smart-phone or personal computer will be provided with a hard copy of the program. The set of nine exercises are performed three times per week for the 12 weeks. Each session takes approximately 30 min to complete. Most of the exercises are performed in a seated position using latex resistance bands wrapped around the toes and/or foot. The exercises target the muscles responsible for ankle dorsiflexion, ankle inversion/eversion, hallux and lesser toe flexion and hallux abduction, and are progressed by either increasing the number of times the exercises are performed (repetitions) or by increasing the level of resistance provided by the bands (light to extra heavy). Adherence to the home-based foot exercise program has been shown to be very high, with 80% of participants (aged 60 to 90 years, 78% women) completing at least 75% of the exercises. The exercises have been shown to increase strength of foot muscles by approximately 20% [22]. Participants will be contacted by the developer of the exercise program ([name]) to address any queries and ensure they are performing the exercises correctly.

**Fig. 2 Fig2:**
[figure not shown]
Intervention footwear (Anodyne #45 Sport Jogger). Image reproduced with permission from Global Footcare, Coomera, Queensland, Australia

**Fig. 3 Fig3:**
[figure not shown]
Intervention foot orthoses (dual-density, three-quarter length Formthotics™). Image reproduced with permission from Foot Science International, Christchurch, New Zealand

Interventions will be administered to both feet, irrespective of whether hallux valgus is unilateral or bilateral. Participants will be free to use additional treatments during the study provided that they are documented in the four-weekly postal surveys. However, participants will be required to withdraw from the study if they report undergoing surgical intervention.

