#### Retention rate

Retention rate is the proportion of recruited participants who complete the 12-week outcome assessment. A ≥ 80% retention rate in each group will be considered acceptable.

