### Secondary outcome: limited efficacy testing

The selection of efficacy outcome measures for this trial is based on expert (OMERACT: Outcome Measures in Rheumatology Initiative) guidelines. The key outcome measure is the pain subscale of the Manchester-Oxford Foot Questionnaire (MOXFQ) [43], which has undergone extensive psychometric validation and is recognised as the best condition-specific outcome measure for hallux valgus [44]. The MOXFQ consists of 16 items reflecting three subscales (pain, walking/standing and social interaction). The pain subscale consists of five items scored on a five-point Likert scale (0 to 4; ‘4’ assigned ‘most severe’; higher scores denoting higher severity). The score for each subscale is calculated as the sum of each individual item score and is expressed on a metric of 0 to 100 (100 times actual score, divided by the maximum possible domain score). The MOXFQ pain domain will be measured at baseline and at four-weekly intervals. The pre-specified primary endpoint will be the 12-week score. The minimum clinically important difference for the MOXFQ pain subscale is 12 points [45].

Other limited efficacy outcome measures will include:(i)the MOXFQ [43] walking subscale, measured at baseline and at four-weekly intervals until 12 weeks;(ii)the MOXFQ [43] social subscale, measured at baseline and at four-weekly intervals until 12 weeks;(iii)foot and ankle muscle strength, measured with a hand-held dynamometer using our previously documented, reliable protocol at baseline and week 12 [46];(iv)general health-related quality of life, assessed using Short Form(SF)-12 [47] measured every four weeks;(v)number of participants using co-interventions, documented every four weeks;(vi)participants’ perception of overall treatment effect, assessed with the question “Overall, how has your foot pain changed since the start of the study?” and using a global impression of change 15-point Likert scale response (ranging from ‘a very great deal worse’ to ‘a very great deal better’), measured at 12 weeks [48].

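### The surgery rule ends outcome collection as well as treatment, so a woman who has surgery loses her 12-week data and counts as not retained

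*Protocol article*

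**What the plan says.** In the protocol article, the Interventions section (paragraph after Fig. 3) treats additional treatments in two ways. In general, "Participants will be free to use additional treatments during the study provided that they are documented in the four-weekly postal surveys". Surgery is the exception: "participants will be required to withdraw from the study if they report undergoing surgical intervention". The withdrawal is from the study, not only from the allocated treatment, and the article describes no follow-up afterwards.

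Two other parts depend on whether such a woman is still assessed:

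- **Retention rate**, a component of the primary feasibility outcome: "Retention rate is the proportion of recruited participants who complete the 12-week outcome assessment", and "A ≥ 80% retention rate in each group will be considered acceptable". No exception is made for withdrawal that the protocol requires.
- **Secondary outcome: limited efficacy testing**, for the MOXFQ pain subscale: "The pre-specified primary endpoint will be the 12-week score". Under Statistical analysis, the baseline-adjusted difference at 12 weeks is to inform the main trial's sample size.

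**The concern.** Surgery during follow-up happens after randomisation and may reflect how well the allocated treatment worked. The Background, describing UK guidance, places surgical referral after non-surgical treatments that were ineffective or a condition that progressed. Ending outcome collection at that event can therefore remove women whose outcomes differ from those of the women who remain, and no later analysis can recover data that were never collected.

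The rule also affects a feasibility measure. Retention is meant to show whether women will stay to the 12-week assessment. A woman who would have attended, but was withdrawn by rule, counts the same as one who stopped responding. The pilot would then understate the retention achievable in a main trial that follows everyone, and the rule could be carried forward into that trial.

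**Working it through.** **Inputs from the article.** Sample size: "The recommended sample size for feasibility and pilot studies is 12 people per group", and "to allow for a 15% drop-out rate, we will recruit 28 participants". Randomisation: "randomise participants on a 1:1 ratio to the control or intervention group". Retention rate: at least 80% in each group.

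**Reproducing the plan's figure.** The target before dropout is 2 × 12 = 24. Dividing by the retained fraction gives 24/0.85 = 28.2. Multiplying up gives 24 × 1.15 = 27.6. The stated 28 agrees with either to within one participant. At 1:1 this is 14 per arm, assuming the final block leaves the arms equal.

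**Losses an arm of 14 can bear.**

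| Losses | Retained | Rate | At least 80%? |
|---|---|---|---|
| 1 | 13/14 | 92.9% | yes |
| 2 | 12/14 | 85.7% | yes |
| 3 | 11/14 | 78.6% | no |

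Each withdrawal after surgery costs 1/14 = 7.1 percentage points in its arm and uses one of two allowable losses. One or two such cases, with no other loss in that arm, still pass.

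**What one case does alongside ordinary dropout.** The article gives no surgery rate, so this is conditional on exactly one woman having surgery before week 12. Assume that the other women drop out independently with probability d, and take d = 5%, 10% and 15% (the last is the planning figure). With X ~ Binomial(n, 1 − d):

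- Unaffected arm: P(X ≥ 12 of 14) = 0.970, 0.842, 0.648.
- Affected arm if she is withdrawn: at least 12 of the other 13 must be retained.
- Affected arm if she is assessed at week 12: at least 11 of the other 13 must be retained.

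Multiplying the two arms gives the chance that both meet the criterion:

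| | d = 5% | d = 10% | d = 15% |
|---|---|---|---|
| No surgery | 94% | 71% | 42% |
| One woman withdrawn after surgery | 84% | 52% | 26% |
| Same woman assessed at week 12 | 95% | 73% | 45% |

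The rule, as opposed to following her, costs about 11, 21 and 19 percentage points respectively (94.6 − 83.9, 72.9 − 52.3, 44.8 − 25.8), but only if a case occurs.

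**The pain comparison.** No figure can be derived. The article gives no surgery rate overall or by arm, no 12-week pain values for women who have surgery, and no SD.

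**The case against.** Several points on the other side stand.

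- **Rarity.** Twelve weeks is short, and the Background speaks of referral, not of operations performed within that time. Few cases, perhaps none, are likely.
- **A reader might infer that surgery makes the retention criterion fail.** It does not: 13/14 and 12/14 both pass, and a third loss in the same arm is needed. What is automatic is only that each woman withdrawn before week 12 counts as not retained.
- **A reader might infer a known bias in the pain difference, larger in the control arm.** The article gives no surgery rate by arm. One could assume that the lost woman's pain is 30 points above the rest of her arm, which moves the arm mean by 30/14 = 2.1 points. But that is her pain had she not had surgery. Follow-up would not recover it, because her 12-week score would include any effect of the operation. The figure also ignores the planned baseline adjustment. It does not measure what the rule costs.
- **Scope of the loss.** The rule is triggered by reporting surgery. Scores collected earlier are not said to be discarded, and surgery first reported at the 12-week visit might not prevent assessment; the text does not say.
- **Choice of question.** Women with previous hallux valgus surgery are excluded at entry, and one may legitimately ask about non-surgical care without surgery. That supports an analysis that leaves out post-surgery values, but it does not require that they go uncollected. Once collected, they allow both analyses.

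The reply that this can be left to the analysis plan does not stand: the protocol itself fixes the rule, and an analysis plan cannot restore uncollected data.

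**Conclusion.** The point holds as a minor design weakness. Read literally, the rule stops outcome collection after an event that the article's own Background connects with unsuccessful non-surgical treatment, and it counts a woman withdrawn before week 12 as a retention loss whatever her willingness.

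Its firm size is one of the two losses an arm of 14 can bear per case. The pass probabilities rest on assumed independent dropout of 5% to 15% and on one surgery occurring. That the missing scores would differ systematically from the others is a reasonable inference, not something the article shows, and neither the direction nor the size of any effect on the 12-week pain difference can be stated. The trial is a pilot without a focus on inferential testing, so the practical effect here is probably small. The rule matters more if the main trial adopts it.

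**What to change.** Separate outcome collection from allocated treatment in the surgery sentence:

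- State that surgery does not end outcome follow-up and that, with the woman's agreement, the remaining outcomes are collected.
- Record the surgery and its date as an intercurrent event, reported separately so that it does not enter the criterion of less than 20% co-intervention use.
- Count her as retained if she is assessed at 12 weeks.
- Report the 12-week pain difference as randomised, and again without post-surgery values.

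Use of the allocated treatment after surgery is a clinical matter for the investigators; this change does not address it.

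**Cost.** A short change of wording and a little extra analysis. The as-randomised result will include any effect of surgery, which is why the second analysis is reported. Timing limits the benefit here: 12-week follow-ups were expected to finish by July 30, 2022, so the last baseline visit would fall about 84 days earlier, near May 7, before the article appeared on June 3. The change could apply only to follow-up still outstanding, and otherwise serves the main trial's protocol.
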